## Abstract

**Background:**

Buprenorphine-naloxone is an evidence-based treatment for Opioid Use Disorder. However, despite its efficacy, nearly half of participants are unsuccessful in achieving stabilization (i.e., period of time following medication induction in which medication dose is adjusted to be effective in reducing cravings/withdrawal, minimize potential side effects, and eliminate illicit substance use). This paper presents the study design and protocol for a digital health intervention designed to promote engagement in and adherence to buprenorphine treatment, offered through an outpatient addiction treatment center, through motivational enhancement and distress tolerance skills training. Personalized feedback interventions represent a promising method to effectively motivate engagement in and adherence to buprenorphine treatment. These interventions are generally brief, individually tailored, and have the potential to be delivered via mobile platforms. Distress tolerance, a transdiagnostic vulnerability factor, has been implicated in the development and maintenance of substance use. Targeting distress tolerance may improve substance use treatment outcomes by promoting the ability to persist in goal-directed activity even when experiencing physical or emotional distress.

**Methods:**

The study aims are to: (1) develop and refine an interactive computer- and text message-delivered personalized feedback intervention that incorporates distress tolerance skills training for persons who have elected to initiate outpatient buprenorphine treatment (iCOPE); (2) examine the feasibility, acceptability, and preliminary efficacy of iCOPE for increasing abstinence, adherence, and retention in treatment compared to a treatment as usual comparison condition; and, (3) examine potential mechanisms that may underlie the efficacy of iCOPE in improving outcomes, including motivation, distress tolerance, self-regulation, and negative affect.

**Discussion:**

Results of this study will be used to determine whether to proceed with further testing through a large-scale trial. This work has the potential to improve treatment outcomes by reducing illicit opioid use, increasing adherence/retention, and preventing future overdose and other complications of illicit opioid use.

*Trial Registration* NCT03842384

## Background

The opioid overdose epidemic continues to surge across the country, resulting in a record number of fatal overdoses in 2017 [1]. With more than 2 million individuals meeting criteria for opioid use disorder (OUD) [2], there is need to expand access to evidence-based treatments. Medications for opioid use disorder (MOUD) is the current gold standard treatment for this population [3]. Of the FDA-approved MOUD, buprenorphine-naloxone (buprenorphine), a long-acting partial opioid agonist, has grown in popularity because of its more flexible administration through office-based programs [4]. Buprenorphine works by reducing cravings, alleviating withdrawal symptoms, and blocking the euphoric effects of opioids [5]. Meta-analyses highlight the effectiveness of buprenorphine in reducing adverse outcomes [6]. However, a significant proportion of patients return to illicit opioid use and/or discontinue treatment before achieving stabilization (i.e., period of time following medication induction in which medication dose is adjusted to be effective in reducing cravings/withdrawal, minimize potential side effects, and eliminate illicit substance use) [5, 7, 8]. This is notable as early lapses are related to poor treatment prognosis and retention [8, 50].

A negative reinforcement model of substance use posits that individuals may use opioids to mitigate aversive internal states [8, 9]. Consistent with this perspective, negative affect has been cited as a primary precipitant of early lapse among opioid users [10]. Distress tolerance (DT), defined as the perceived or actual ability to handle uncomfortable physical or emotional states, is a transdiagnostic vulnerability factor implicated in the development and maintenance of affective symptoms/disorders and substance use [11, 12]. DT involves the ability to withstand negative reinforcement opportunities by exerting control over behavioral responding that would otherwise provide immediate relief from distress [13]. DT is inversely related to a range of drug use outcomes, including frequency and severity of use [14, 15], premature termination of treatment [16], and early lapse/relapse [17, 18]. Preliminary work suggests that addressing DT during substance use treatment may improve outcomes by promoting the ability to persist in goal directed activity even when experiencing distress and discomfort [19].

Personalized feedback interventions (PFI), such as decisional balance feedback, represent a promising method to effectively motivate engagement in and adherence to buprenorphine treatment, particularly among individuals characterized by low DT. Decisional balance feedback involves an evaluation of the advantages/disadvantages of engaging in a certain behavior (e.g., opioid use), compared to the advantages/disadvantages of an alternative behavior (e.g., abstinence), and also offers strategies for changing problematic behavior (e.g., DT skills training) [20, 21]. Although PFIs have shown promise for reducing substance use across a variety of adult populations [21, 22], no integrated protocols exist to enhance motivation and facilitate DT skills training among individuals with OUD.

Given that negative internal states may occur in participants’ natural environments in response to drug cues, stressors, or the context of withdrawal, this population may benefit from a motivational and DT-based intervention that can be delivered on a mobile platform. In the United States almost 95% of adults own a mobile phone [23]. Text message interventions have demonstrated efficacy for health promotion and behavior change, with personalized messages showing the greatest benefit [24]. These platforms also offer the advantage of being delivered outside of structured treatment sessions and allow for the content, timing, and frequency of messages to be individually tailored to times when certain skills and motivational reminders are most salient [25].

This paper describes the study design and procedures for a behavioral treatment development trial that examines the feasibility, acceptability, and preliminary efficacy of a digital health intervention (iCOPE) designed to promote engagement in and adherence to buprenorphine through motivational enhancement and DT skills training among individuals initiating outpatient addiction treatment.

## Methods

### Study design overview

The current study meets the objectives of Stage I of the NIDA Behavioral Therapies Development Program, which provides a conceptual framework grounded in basic science, for intervention development [26]. Stage I includes two phases—Stage 1A and Stage 1B. Stage 1A involves the creation of a new intervention, while Stage 1B establishes feasibility through pilot testing [26]. In Phase 1 (Stage 1A), our team will develop and refine, through formative evaluation, an interactive computer- and text message-delivered PFI that incorporates DT skills training for persons who have elected to initiate outpatient buprenorphine (iCOPE). Specifically, this intervention is designed to promote medication induction and stabilization following standard clinic intake procedures. All participants will receive standard outpatient buprenorphine treatment, including medication visits, counseling, case management, and peer recovery (treatment as usual; TAU). In Phase 2 (Stage 1B), we will conduct a pilot randomized controlled trial. Eighty patients with a history of OUD, actively seeking outpatient buprenorphine, will be randomly assigned to iCOPE or TAU, using a 3:1 randomization ratio. We propose a 3:1 randomization ratio to maximize the information gained about the iCOPE intervention while including a comparison condition. All participants will complete assessments at treatment initiation as well as 1-, 4-, 8- and 12-weeks post-initiation. These data will be used to inform the development of a large-scale, fully-powered trial. At the time of this report, recruitment for Stage 1A is ongoing.

### Stage 1A

Qualitative, in-depth, individual interviews are currently being conducted with patients actively engaged in buprenorphine treatment (target *N* = 24). The sample is balanced by gender, primary type of opioid use (prescription pills; heroin), and phase of recovery [early (≤ 8 weeks of treatment) vs. late (> 8 weeks of treatment)]. Interviews will continue until saturation is achieved. Following informed consent, demographic and clinical data are obtained. Interviews are conducted by the Principal Investigator ([name]) or a trained Research Assistant, and follow a semi-structured interview protocol that stems from primary research questions and project goals. Specific questions focus on participants’ use of computers, mobile phones, and other technologies; prior engagement in MOUD; barriers/facilitators to engaging in MOUD; reactions to and perceived usefulness of proposed intervention; and preferences, benefits, and likelihood of engaging in digital health interventions. All interviews are conducted in a private office to ensure confidentiality and are digitally recorded. Each interview takes approximately 60–90 min to complete; participants receive a $30 gift card for their time/effort. Interviews are transcribed by a professional agency, and the written transcripts are later reviewed to resolve discrepancies.

Qualitative analyses will be conducted to inform intervention development and refinement. Both thematic (deductive) and data driven (inductive) codes will be utilized. Deductive codes will be drawn from the topics in questions used to facilitate the interviews; inductive codes will capture additional concepts that emerge from the participants. Early interviews will be coded by three team members, until stability of the coding structure is reached. All interviews thereafter will be independently coded by two team members using the coding scheme, then compared to ensure agreement. Agreed upon codes will be entered into NVivo. Throughout the process, a framework matrix will be created. This data reduction tool, a matrix of cases and themes based on interview debriefs and individual interview codes, will be used to track emergent ideas and concepts that impact intervention design and future interviews [27–29]. After every few interviews, research team members will examine the framework matrix, identify reoccurring major themes, make changes to intervention content as appropriate, then test the edits in subsequent interviews. This method will allow for quick, iterative turnaround of participant feedback to intervention edits and modifications of interview questions.

We will further refine the intervention by recruiting an additional 16 participants for open pilot testing. These participants will be in the initial 8 weeks of treatment and will be balanced by gender and primary type of opioid use. At the end of the iCOPE intervention, semi-structured interviews, in combination with measures of protocol adherence, will be used to evaluate and then improve upon the intervention’s appropriateness and comprehensibility. During the interviews, participants will be queried about their comfort with technology (computer and text message); ease of using the technology formats; level of understanding of intervention content; perceived usefulness of material; satisfaction with format and content; likelihood of recommending the intervention; likelihood of continued use; and suggestions for improvement. To guide refinements, we will collect data on the feasibility and acceptability of the intervention. Feasibility will be determined by assessing study recruitment and refusal rates, intervention completion, follow-up rates, and rates of study attrition. Acceptability will be determined by the (a) System Usability Scale, a participant-completed, reliable and valid metric for measuring usability and acceptability of technologies; [30–32] and (b) Relative Subjective Count, the quotient of the participant’s estimate of the number of times the system delivers a text, divided by the number of texts actually delivered [33]. All proposed changes will be integrated into the final version of iCOPE for testing in Phase 2.

### Stage 1B

Stage 1B will employ a randomized controlled trial design to pilot test iCOPE relative to the TAU control condition (see description of treatment conditions below). Adult patients (*N *= 80) meeting eligibility criteria will be randomly assigned to either the iCOPE or TAU conditions.

Following the initial evaluation, in which patients are admitted to buprenorphine treatment, staff will refer potentially eligible patients to study personnel. Interested participants will meet with study personnel in a private setting at the clinic. Informed consent will be obtained, and final eligibility will be determined. Eligible participants will complete a baseline assessment, including two brief behavioral measures of DT (Mirror Tracing and Breath Holding; see Assessments). Participants will then be randomly assigned to iCOPE or TAU. Participants in the iCOPE condition will complete the brief computerized intervention. They will also be informed about the text message element of the intervention and instructed in these procedures. We will recruit 80 participants who will be assigned to condition at a 3:1 ratio, with 60 participants assigned to iCOPE and 20 participants assigned to TAU. Participants will be scheduled to return to the clinic for follow-up appointments consisting of an online survey, behavioral DT measures, and urine collection. Follow-ups will occur at 1-, 4-, 8- and 12-weeks post-treatment initiation.

### Participants

Participants will include 80 males and females between the ages of 18 and 75 initiating OUD treatment, specifically the use of buprenorphine. For inclusion, participants must meet current Diagnostic and Statistical Manual of Mental Disorders, 5th Edition (DSM-5), criteria for OUD and have access to a cell phone with text message capability. To reduce the risk of adverse events and potential confounds, we will employ the following exclusion criteria: (1) active suicidality and/or psychosis that would interfere with the ability to participate in the intervention, (2) not fluent in English as translation is beyond the current study resources, and (3) limited mental capacity or inability to provide informed written consent.

### Study setting

The Lifespan Recovery Center at Rhode Island Hospital will serve as the proposed recruitment site. The Lifespan Recovery Center is an outpatient addiction treatment program that offers buprenorphine and ancillary services (e.g., counseling, case management, peer recovery). The clinical team includes: four physicians, four therapists, a case manager, and a peer recovery specialist. On average, there are approximately 20 new patient admissions per month. As part of routine clinical care at the Lifespan Recovery Center, patients typically attend an intake evaluation and medication induction appointment, followed by weekly follow-up visits for the initial 8 weeks of treatment (stabilization). Once stabilized, patients continue to attend monthly follow-up appointments for the duration of treatment.

### Compensation and retention

In an effort to bolster study retention, we have aligned study follow-up assessments with routine clinic visits. Additionally, follow-up reminders will occur via emails, telephone calls, and text messages. Participants will earn a $25 gift card for completing the initial assessment and a $20 gift card for completing each follow-up assessment. Participants completing all required follow-ups will earn an additional $25 gift card. Participants have the potential to earn up to $130 for completing all study assessments.

## Intervention conditions

### iCOPE

iCOPE will involve two delivery modes: computer and text message (see Fig. 1). The proposed intervention will initially target motivational processes in combination with introductory strategies for managing physical and emotional distress through a single, brief, computer-delivered, session followed by 8 weeks of theoretically-informed text messages intended to enhance motivation and promote DT (see Table 1).

**Fig. 1 Fig1:**
[figure not shown]
Overview of Proposed iCOPE Intervention

**Table 1 Tab1:** Description of iCOPE treatment content

Intervention type	Computer intervention components	Text message intervention components
PFI	Evaluate advantages and disadvantages of behavior change	Reminders of the advantages of behavior change elicited during initial intervention
	Elicit recognition of problem and motivating factors for change	Reminders of personal motivators
	Assist with setting personal change goals for opioid use and treatment	Reminders of personal goals
DT	Acceptance: education on meaning of acceptance; strategies to promote acceptance of reality	Acceptance: encourage acceptance-based strategies to use in moments of distress
	Self-soothing: education on using five senses to comfort self during times of distress	Self-soothing: suggestions of ways to comfort self during times of distress
	Distraction: education on using distraction skills to change emotional response to distressing stimuli	Distraction: reminders of distraction strategies to change emotional responding
	Improving the moment: education on methods to replace immediate negative events/states with more positive ones	Improving the moment: encourage methods to replace negative with positive states

*PF* personalized feedback, *DT* distress tolerance

The initial intervention phase will be delivered via computer following routine intake procedures at the recruitment site. We elected to have participants complete the computer-based intervention on-site, instead of allowing participants to complete independently on their own device, to optimize fidelity of the intervention given that it is a Stage 1 trial. We will evaluate participant preference for computer delivery in the open pilot trial to determine if expanding the intervention to home devices is warranted in the future. iCOPE will be presented in a way that encourages participants to be mindful of their behaviors in a non-confrontational manner. The intervention has two aims: (a) engage patients in a decisional balance exercise designed to evaluate the perceived advantages/disadvantages of making a behavior change (abstinence from opioids, adhering to buprenorphine) to enhance motivation and (b) provide concrete strategies to better tolerate emotional and physical discomfort to persist with identified behavioral goals while initiating treatment. First, participants will be guided through a decisional balance exercise and queried about perceived barriers to treatment. Next, this information will be summarized to deliver feedback about personal motivators and recommended DT coping skills.

The second intervention phase will be delivered via text message and will focus on (a) promoting motivation for abstinence over and above the reinforcing effects of opioids and (b) emphasizing adaptive strategies for tolerating physical and psychological discomfort. To do this, text messages will be strategically delivered during the initial 8 weeks of stabilization which are considered a “high-risk” period (see Fig. 1). The text messages will be personalized in nature and offer skills training (reminders of previously learned DT skills) and motivational messages (content directly derived from decisional balance exercise; see Table 1). The frequency and timing of text messages will be determined through prior formative work; however, we anticipate sending at least two automated text messages each day. A variety of messages will be delivered throughout the eight-week period and will create (a) a natural progression in skill-building, (b) continued motivation for engagement, and (c) responsiveness to participants’ needs through personalization. We will create a variety of text messages that provide concrete DT skills as well as personalized messages reminding participants of their identified goals and personal motivators (e.g., health, family, finances). Further, we anticipate providing participant-driven text messages to provide tailored support in the moments needed. For example, if a participant texts “CRAVING” or “STRESS” to the automated program, indicating the need for additional support on that topic, the participant would receive a relevant skills-based message. Messages will be delivered to participants’ personal cell phones using an automated computerized system based upon pre-specified delivery algorithms [34, 35].

### Treatment as usual (TAU)

The TAU condition will consist of comprehensive outpatient buprenorphine treatment, including medication management, counseling, case management, and peer recovery. TAU was selected as the comparison condition as it represents a robust and evidence-based approach to the treatment of OUD. The goal of this phase of treatment development is to evaluate the initial feasibility, acceptability and preliminary efficacy of the proposed intervention through a small pilot trial. Decisional frameworks used to select an appropriate control condition for randomized controlled trials for behavioral interventions suggest that at earlier stages of treatment development it may be favorable to select a TAU condition. Inclusion of a rigid control condition (e.g., health education condition) could result in the underestimation of the effect size and yield null findings in a trial with insufficient statistical power to detect effects [36]. TAU is currently the gold standard of care for treating this population, and therefore, an adequate control condition for this stage of development and evaluation.

## Assessments

### Diagnostic and screening assessment

During routine clinic procedures, patients are evaluated for the presence of DSM-5 OUD, active suicidality and/or psychosis, and interest in initiating buprenorphine through a shared decision-making process. A Demographic-Treatment History Questionnaire will assess gender, age, race/ethnicity, education, occupation, income, substance use treatment history, and access to a cell phone with text message capability (see Table 2).

**Table 2 Tab2:** Overview of timing of measurement

Measure	Intake	1- Week	4- Weeks	8- Weeks	12- Weeks
Demographics–treatment history	X				
Distress tolerance scale	X	X	X	X	X
Mirror-tracing persistence task	X	X	X	X	X
Breath-holding task	X	X	X	X	X
Difficulties with emotional regulation scale	X	X	X	X	X
UPPS-P impulsive behavior scale	X	X	X	X	X
Positive affect negative affect schedule	X	X	X	X	X
Decisional balance scale	X				
Timeline follow-Back	X	X	X	X	X
Urine toxicology screens	X	X	X	X	X
Readiness ruler	X	X	X	X	X
Client satisfaction questionnaire	X			X	
System usability scale				X	
Relative subjective count				X	

### Primary outcome

The primary outcome of this study is percentage of days positive for drug use in between assessments (self-report and biochemically verified; see Table 2). The interviewer-delivered Timeline Follow-Back will assess daily opioid use, other illicit substances (e.g., cocaine), and alcohol use. It has demonstrated good reliability [37] and has been validated for the assessment of opioids and other substance use [38]. Urine Toxicology Screens will be administered at all time points to screen for the presence of opioids and other illicit substances.

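### Most days in the primary outcome rest on participants' own report, only iCOPE adds abstinence reminders, and no stated analysis would show whether reporting accuracy differs by arm

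*Protocol article*

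**What the plan says.** Under Primary outcome, the Protocol article defines the endpoint as "percentage of days positive for drug use in between assessments (self-report and biochemically verified; see Table 2"). Two sources feed it. The daily source is self-report: "The interviewer-delivered Timeline Follow-Back will assess daily opioid use, other illicit substances (e.g., cocaine), and alcohol use". The objective source is intermittent: "Urine Toxicology Screens will be administered at all time points to screen for the presence of opioids and other illicit substances". Stage 1B gives the schedule: "Follow-ups will occur at 1-, 4-, 8- and 12-weeks post-treatment initiation". It also gives the allocation: "assigned to condition at a 3:1 ratio, with 60 participants assigned to iCOPE and 20 participants assigned to TAU".

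The arms differ in what participants are told and sent. Of iCOPE participants, Stage 1B says: "They will also be informed about the text message element of the intervention and instructed in these procedures". The iCOPE section gives as one of two aims of the texts "promoting motivation for abstinence over and above the reinforcing effects of opioids"; the other is coping with discomfort. On frequency it says "we anticipate sending at least two automated text messages each day", with the final frequency left to formative work. Texting lasts 8 weeks, and Table 1 mixes goal and motivator reminders with distress tolerance skills. The TAU section describes no such messages, although both arms receive counseling, case management and peer recovery.

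The Data analysis section lists preliminary checks of missing data, dropout, distributions and correlations among outcomes. It then describes one model fitted to an intent-to-treat sample and to an as-treated sample. It states no comparison of self-report with urine by arm, and no arm comparison resting on urine alone.

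**The concern.** A percentage of days needs a value for every day, and only the Timeline Follow-Back supplies one. Urine can confirm or contradict the last few days before a visit, but not the weeks between visits.

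Participants cannot be masked to a text-message program. Those in iCOPE set personal goals for opioid use and are reminded of them; those in TAU are not, on the article's description. If this changes how fully people disclose use, the arm difference in reported days mixes a change in behavior with a change in reporting. Randomization does not protect against this, because the difference arises after assignment and through the measurement.

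The article takes similar results in the two analysis samples as grounds for more confidence. Both samples use the same reported outcome, so they would share any reporting bias, and their agreement says nothing about it. At stake is the effect estimate that helps decide whether to go on to a full-scale trial. Adherence, a secondary outcome, also draws on the Timeline Follow-Back.

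**Working it through.** **Inputs from the article.** N = 80 at 3:1; follow-ups at weeks 1, 4, 8 and 12; urine at each; texting for 8 weeks.

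**Assumptions, not in the article.** A urine detection window of 2 to 4 days; true use on 30% of days in both arms; reporting rates as stated below; no over-reporting.

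**1. The article's own figure.** 80 × 3/4 = 60 and 80 × 1/4 = 20. The split reproduces.

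**2. What urine can verify.** The intervals are 7, 21, 28 and 28 days, together 84. Coverage = 4 screens × window / 84.
- 2 days: 8/84 = 9.5%.
- 4 days: 16/84 = 19%.

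Weighting the four intervals equally instead, as a repeated-measures model might, gives a mean coverage of 13% (2 days) to 26% (4 days). Week 1 is covered best (2/7 = 29% to 4/7 = 57%) and each 28-day interval worst (7% to 14%). Either way, most days rest on report.

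**3. When the arms differ in exposure.** Texts run for 56 of 84 days. They cover the intervals ending at weeks 1, 4 and 8, but not the last 28 days.

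**4. What differential reporting would do.** Reported share = true share × proportion of use days reported. TAU at 90%: 0.30 × 0.90 = 0.27.

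| iCOPE reports | Reported share | Difference | Odds ratio |
|---|---|---|---|
| 90% | 0.27 | 0 | 1.00 |
| 80% | 0.24 | −3 points | (0.24/0.76)/(0.27/0.73) = 0.85 |
| 70% | 0.21 | −6 points | (0.21/0.79)/(0.27/0.73) = 0.72 |
| 60% | 0.18 | −9 points | (0.18/0.82)/(0.27/0.73) = 0.59 |

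The direction is not fixed. If TAU reported 80% and iCOPE 90%, the odds ratio would be (0.27/0.73)/(0.24/0.76) = 1.17, and a true benefit would be hidden.

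**5. How far urine repairs it.** Suppose every day inside a window is corrected. With f the fraction covered and s the reporting rate, reported share = 0.30 × [f + (1 − f) × s]. For 90% against 70%:
- 2 days: 27.3% against 21.9%, odds ratio 0.75.
- 4 days: 27.6% against 22.7%, odds ratio 0.77.

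Uncorrected it was 0.72, so even complete verification inside the windows removes little of the bias.

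**6. How precise a check by arm would be.** At one visit, with all 60 and 20 providing data and discordance d in both arms, the half-width of the 95% interval for the arm difference is 1.96 × √[d(1 − d)(1/60 + 1/20)].
- d = 10%: 15 points.
- d = 20%: 20 points.

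Restricted to urine-positive visits it is wider. If 30% were positive (18 and 6 participants, an assumption), d = 20% gives 1.96 × √[0.16 × (1/18 + 1/6)] = 37 points. Pooling visits helps, but the check remains descriptive.

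**7. Why the denominator matters.** Take discordance as a share of all visits. Use at 50% of visits with 90% reported gives 0.50 × 0.10 = 5%. Use at 25% with 80% reported gives 0.25 × 0.20 = 5%. Equal rates can hide unequal candor when use itself differs. Among urine-positive visits the same cases give 10% and 20%.

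**The case against.** The strongest reply is that the article does plan an objective check: the outcome is biochemically verified, with urine from both arms at every time point. That stands, and it would be wrong to say that the outcome is self-report alone. Steps 2 and 5 show why the check is partial.

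A reader might also infer that iCOPE participants are texted their abstinence goals every day and will therefore under-report. The article does not support this. The frequency is only anticipated, the content is mixed, and texting stops at week 8. TAU counseling may also create pressure to report abstinence. iCOPE is described as non-confrontational and invites participants to text when craving, so greater candor is equally conceivable. What stands is the possibility of a difference, not its sign.

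Third, the sizes in step 4 are assumed, and random error is large: with an assumed SD of 20 to 40 points, the standard error of the arm difference at one visit is SD × √(1/60 + 1/20), about 5 to 10 points. The 3-point bias is below one standard error. That limits the practical weight of the point, but random error does not cancel a bias. The article also warns against over-reading small pilots, and retention comes from clinic records, so the overall pattern of results does not hang on self-report alone.

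Finally, an agreement table or masked interviewing could sit in an analysis plan or full protocol not shown here. The absence from the article is therefore weak evidence. What does rest on the article is that the endpoint is a day count, the daily data are self-reported, and the two analyses described share that outcome.

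**Conclusion.** The point holds as a design weakness worth correcting, not as an error or a demonstrated bias. The primary outcome relies on report for most of its 84 days: about 81% to 90% under a 2-to-4-day window. The arms differ in abstinence-oriented contact, and neither analysis described could separate better reporting from less use, or the reverse. If reporting differed by 10 to 20 percentage points at 30% true use, the spurious odds ratio would be about 0.85 to 0.72 if iCOPE under-reports more, and above 1 if TAU does. These rates are assumptions, and the article gives no basis for preferring one.

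The article does not support concluding that a favorable iCOPE result would be false.

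**What to change.** 1. **Visit procedure.** At each follow-up, collect urine first. Then run the Timeline Follow-Back with an existing team member who did not deliver that participant's session and is not told the arm. Reconcile the mode at the same time: Stage 1B lists an online survey at follow-up, while Primary outcome calls the Timeline Follow-Back interviewer-delivered.
2. **Agreement by arm.** Report by arm and visit, and pooled over visits, the share of urine-positive visits at which use in the detection window was denied. Give 95% intervals that allow for repeated visits, and state the window for each substance.
3. **Sensitivity analyses.** Compare urine-positive screens by arm with the same GEE approach. Also show the primary effect over a stated range of differential reporting in both directions, for example iCOPE-to-TAU reporting ratios from 70/90 = 0.78 to 90/70 = 1.29. Present both whatever the observed discordance. A trigger based on an observed difference would fire on noise with 20 TAU participants.

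**Cost.** A fixed visit order, a rota among present staff, and a table and two analyses from data already collected. The procedural part must be settled before Stage 1B visits begin, because it cannot be repaired at analysis; at the time of the article, only Stage 1A was recruiting.

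**Downsides.** Participants may reveal their arm, so masking will be incomplete. The agreement table is imprecise and descriptive only. The urine-only comparison answers a narrower question, recent use at visits.
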